### Study Procedures

Demographic data (age, sex, ethnicity, skin tone [Fitzpatrick 6-point scale [24] ranging from type 1 for skin that always burns to type 6 for skin that never burns]) are recorded on an electronic case report form using the Castor electronic platform. Medical history questions are limited to the presence or absence of conditions that might affect skin perfusion and pigmentation, cardiovascular processes, and any prescription medicines for these conditions.

The study staff records a set of premeasurement observations and the presence or absence of sweat on the participant’s face; any facial hair on the cheeks; tattoos, jewelry, birthmarks, scars, or other features on the face; the use of foundation or concealer; and the position of the participant (seated, prone, supine or lying on one side).

Patients may also be recruited into 1 of 3 subprotocols depending on premeasurement observations (Table 1).

The study staff ensures that participants have been at rest for at least 10 minutes before VS measurement starts (which can include the period of data collection described previously).

**Table 1 table1:** Subprotocols.

	Subprotocol	Description
1	Blood pressure measurement	Blood pressure will be measured at the same time as other vital signs using standard of care equipment (sphygmomanometer) in participants who are able to cooperate and stay relatively still
2	Electrocardiogram	A 3-lead electrocardiogram will be recorded to assess heart rate variability in a representative subset of participants (based on age, skin tone, and illness; see Table 3)
3	Questionnaire	Guardians, parents, or carers and children will be asked to complete a questionnaire about their preferences for Lifelight-type technologies versus standard of care methods for measuring vital signs

In each study session, VS is measured as per the subprotocol using the SOC equipment, while simultaneously capturing a video of the participant’s face using the Lifelight Data Collect app running on a tablet (standard iPad). This app is a research tool that captures and uploads video data to secure cloud storage for research purposes only and is distinct from the CE-marked Lifelight medical device developed from data collected from previous studies. The Data Collect app does not display any VS estimates and is not used for clinical interpretation or analysis.

In each study session, at least 2 VS (PR, oxygen saturation, RR) and temperature are measured twice over a 60-second period using SOC equipment and methods.

A standard clinical finger clip sensor for the measurement of oxygen saturation and PR is placed on a finger. Oxygen saturation and PR are measured at 0, 30, and 60 seconds of the recording period and averaged.

RR is determined by counting chest rises throughout the 60-second period. The nurse may place their hand on the participant’s chest to improve the accuracy of counting while being mindful not to obscure the camera’s line of sight.

At the same time, a video of the participant’s face (and torso in children younger than 5 years of age) and audio is captured for up to 3 minutes using the Data Collect app running on a tablet positioned approximately 1 meter away and angled toward the participant’s face. Background luminosity is measured automatically. Recording is started and stopped by the research nurse via the iPad.

A maximum of 3 attempts at recording measurements is made. Once measurements have been completed, the study staff fill in postmeasurement questions relating to how much the participant moved, their position, whether they were wearing glasses, any hairstyle or other item (eg, face covering) that obscured any part of their face during the recording, and whether the app reported “face not found” at any point during the recording.

A questionnaire is also available to garner feedback on the technology from the clinical user’s point of view (ie, the nurses who take the VS measurements). Questionnaire data are fully anonymized and recorded without any identifiable information.

Each study session, including approaching the participant, obtaining consent, and performing the study procedure takes about 30 minutes. Participants were not followed up after the VS measurements but continued to receive clinical care as appropriate for their condition.

### Subprotocols

Participants are recruited into 3 subprotocols as appropriate (Table 1). Subprotocols 1 and 2 may be run concurrently with the main protocol if the research nurse considers it practical to also record BP and an electrocardiogram (Figure 1).

**Figure 1 figure1:**
[figure not shown]
Study flow and data collection. BP: blood pressure; ECG: electrocardiogram.

### Ethical Considerations

The study is being performed in accordance with the spirit and the letter of the Declaration of Helsinki, the Good Clinical Practice Guidelines, and the protocol and applicable local regulatory requirements and laws. The VISION-Junior protocol was approved by the Health Research Authority and Health and Care Research Wales (IRAS reference 321956) and the Newcastle North Tyneside Research Ethics Committee on March 30, 2023. Informed consent is obtained electronically using Castor eConsent, a secure NHS-compliant platform. Informed consent is provided by participants aged 16 years and older and by the parent, guardian, or carer of younger children. Children younger than 16 years of age are also given the opportunity to sign an assent form. As the study is noninterventional, participants will not receive financial compensation for participation but may be offered small incentives such as stickers or certificates. Participation in the study is entirely voluntary, and participants may withdraw from the study at any time. Specific, explicit written consent was obtained from all individuals featured in the videos provided in Multimedia appendices 4 and 5, permitting use for publication purposes.

### Privacy and Data Collection

Each study participant is assigned a unique sequential patient identifier; no identifiable data are stored. All documents are stored securely and can only be accessed by study staff and authorized personnel. The code linking the patient identifier to their personal information is kept within the hospital study site and can only be accessed by the research team within that site.

For each reading, a high-quality video of the face (and torso in young children) and an audio file are saved to the internal storage of the iPad in encrypted form and transmitted directly to the sponsor’s NHS-compliant cloud server. Files were automatically deleted following upload to the server.

All data collected about participants during the study will be kept strictly confidential and handled according to the General Data Protection Regulations. Videos and audio recordings collected during the study constitute personal data as it may be possible to identify participants. Full-resolution, full-face, or torso video data are required to develop Lifelight Junior into a clinically useful device; the analysis cannot be performed using blurred videos. The data collected for research purposes only (not clinical care) are processed within the legitimate interests of Xim Ltd.

### Data Handling

Analysis of the videos uses the encrypted files, which, in most cases, are processed automatically within a secure cloud infrastructure (ie, without any person viewing the videos); in rare cases, it may be necessary to analyze a video manually if the recording is not as expected. The analysis results in anonymized aggregate datasets. No decrypted files are stored at any point in the processing. The electronic case report forms are stored and managed using the Castor electronic cloud.

### Performance Targets

While Lifelight is certified as a class I CE medical device [18], the performance of Lifelight Junior needs to be appropriate for routine clinical practice in pediatric patients. Table 2 lists the performance targets for Lifelight Junior for measuring VS in pediatric patients; training data collected during VISION-Junior will support progress toward these targets.

**Table 2 table2:** Performance targets in VISION-Junior.

Vital sign	Performance target	Reference
Pulse rate	Root mean square error ≤5 beats per minute	[25]
Respiratory rate	Maximum error of 5 breaths per minute for 100% of measurements	Minimum standard met by all approved respiratory monitors
Oxygen saturation	Maximum error tolerance 4%	[26]

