The VISION-Junior study explores the measurement of VS using a Lifelight app developed for pediatric patients (aged 18 years or younger) attending the pediatric emergency department. As in VISION-MD in adults, high-resolution full-face videos will be recorded. In younger children (younger than 5 years of age), the video will also include the torso to increase the surface area from which the signal is recorded, and because the torso is likely to move less than the face. Audio data will also be recorded, as crying, wheezing, coughing, and other sounds can also predict illness in children [22,23].

The aim of the VISION-Junior study is to assess whether the app can be used to accurately measure VS in pediatric patients. This protocol describes the collection of data that will initially be used to develop the algorithms for the measurement of VS in children. Later data will be used to assess the accuracy of the app across the range of VS values encountered in children of different ages. The objectives are as follows.

The primary objective is to collect data to support the development of the app for the accurate measurement of PR, RR, and oxygen saturation in pediatric patients and to assess the accuracy of measurements against SOC methods. Secondary objectives are: (1) to assess—using the collected PPG data—whether other (direct or indirect) measurements can be made using the app, including temperature, BP, PR variability, and audio analysis; (2) to evaluate the impact of subject-specific variables on the PPG VS measurements (eg, medication, cosmetics, facial or body hair, and skin tone); (3) to obtain data to understand patient and parent or guardian or carer habits and preferences for VS measurement using questionnaires (Multimedia Appendices 1 and 2); and (4) to assess the usability of Lifelight Junior for measuring VS in pediatric patients through questionnaires completed by participating health care professionals (Multimedia Appendix 3).

Most of the data collected in the study will be used to train the app algorithms to measure VS in pediatric patients. The remaining data will be kept separate and used to assess the accuracy of the algorithms at regular intervals during the data collection period. The study delivery process will be responsive to this learning curve to increase the likelihood that the predetermined accuracy target for each VS estimation is achieved by the study end.

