### Sample Size

An estimated 500 pediatric patients (18 years old or younger) will be recruited into the study. This sample size is informed by the previous VISION-D, VISION-MD, and VISION-Acute studies [17,21]. However, the sample size cannot be formally calculated because it depends on the incremental improvement in the performance of the app achieved through machine learning using the training data generated early in the study. The split between training and testing data will be determined during the study according to the quality of the data collected. The study management team monitors the progress of data collection and accuracy and updates the study teams weekly. The study will continue until the accuracy of the app for measuring VS in pediatric patients is sufficient for various clinical use cases.

In addition, recruitment targets according to age, sex, Fitzpatrick skin tone, and medical history have been defined, as shown in Table 3, to ensure accuracy in a broad range of clinically relevant patients.

**Table 3 table3:** Demographic and medical history recruitment targets.

	Targets
Age	≥12% aged 0-1, 1-2, 2-5, 5-11, 11-14, 14-18 years
Sex	≥40% male; ≥40% female
Skin tone	15% of participants will have Fitzpatrick skin tones 4, 5, or 6 (this is not a hard target as achieving this figure depends on the demographic diversity of the study region)
Medical history	≥40% in each of the following categories: Febrile (≥38 °C) Afebrile Ill (as judged by the clinical staff); to ensure a spread of conditions, no more than 50% of recruited patients will have an acute respiratory illness (eg, bronchiolitis, asthma, virus-induced wheeze, pneumonia, and croup) Well, including pediatric patients with a minor injury

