## Results

The study started on June 12, 2023, and as of December 20, 2023, had recruited 303 participants. The study was extended until the end of March 2024 to enable the target recruitment (500) to be met; 532 participants had been recruited as of April 5, 2024.

Data are currently being used for machine learning to refine the algorithms to improve clinical accuracy. We anticipate that final analyses to determine the performance of the app against the targets set out in Table 2 will be complete by mid-August 2024. The performance of the app will be determined across the range of VS values encountered in children in clinical practice by comparing the VS values recorded using PPG versus standard methods.

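### The respiratory-rate target is a zero-failure rule that gets harder to meet as the test set grows, the test-set size is left open, and the stated pass rule does not fit it

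*Protocol article*

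**What the plan says.** Three parts of the protocol article bear on the RR verdict.

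- **Performance Targets, Table 2.** The RR target is "Maximum error of 5 breaths per minute for 100% of measurements". Its stated basis is a minimum standard that all approved respiratory monitors meet. No number of test readings and no confidence level is attached.
- **Sample Size.** Recruitment is set at about 500 children without a formal calculation, because "the sample size cannot be formally calculated because it depends on the incremental improvement in the performance of the app". On the test set: "The split between training and testing data will be determined during the study according to the quality of the data collected". The Introduction adds that "Most of the data collected in the study will be used to train the app algorithms", and that the held-out remainder is used to check accuracy at regular intervals while data are still being collected.
- **Data Analysis.** A target counts as met when the mean error and SD of the app's measurements are no worse than the Table 2 value. Missing, implausible or problematic readings are left out; the article does not define the last two.

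On the reference method, Study Procedures states that "RR is determined by counting chest rises throughout the 60-second period". The same section has at least two of the vital signs measured twice per session, and allows up to three recording attempts.

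**The concern.** A sample maximum does not estimate accuracy in the way a mean, an SD or a proportion does. It can only rise as readings are added. A criterion that no reading may exceed 5 breaths/min therefore penalises a larger test set, although a larger test set is better evidence. Because the size of the test set is to be decided during the study, a quantity that affects the chance of meeting the target is not fixed in advance.

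The Data Analysis rule does not settle this. Table 2 gives RR a limit on individual errors and a coverage of 100%. It gives no value for a mean error or an SD. A reader cannot tell which rule decides, and the two can disagree sharply.

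Assessing RR accuracy is part of the primary objective, so this affects one of the three main accuracy results.

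**Working it through.** **Inputs from the article.** Error limit 5 breaths/min, no exceedance allowed (Table 2). Planned recruitment 500 (Sample Size); by the Results section, "532 participants had been recruited as of April 5, 2024". If most data go to training and the split is by child, the test set holds fewer than 250 of 500 children, or fewer than 266 of 532. The sizes 50, 100 and 250 therefore span the plausible range. The article states no test-set size and no probability of meeting the target, so there is no figure of its own to reproduce.

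**Assumptions.** Errors (app minus manual count) are independent and normal with mean 0. The SD is not in the documents and is varied.

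**Step 1: chance of meeting the Table 2 rule.** The chance that one reading falls within the limit is p = 2Φ(5/SD) − 1. The chance that all n do is pⁿ.

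| Error SD | p | n = 50 | n = 100 | n = 250 |
|---|---|---|---|---|
| 1.25 | 0.99994 | 99.7% | 99.4% | 98.4% |
| 1.5 | 0.99914 | 95.8% | 91.8% | 80.7% |
| 1.8 | 0.99453 | 76.0% | 57.8% | 25.4% |
| 2.0 | 0.98758 | 53.5% | 28.7% | 4.4% |
| 2.5 | 0.95450 | 9.8% | 1.0% | <0.1% |

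Dependence on n is weak at SD 1.25 or less and strong between about 1.5 and 2.0. At 2.5 failure is likely at any of these sizes. Correlated repeat readings within a child would slow the fall but not reverse it.

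**Step 2: what a clean result shows.** With no exceedance in n independent readings, the one-sided 95% upper bound on the exceedance rate is 1 − 0.05^(1/n): 5.8% at n = 50, 3.0% at 100 and 1.2% at 250. Showing at least 99% within the limit needs ln 0.05 / ln 0.99, rounded up to 299 readings without an exceedance. No finite number shows 100%.

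**Step 3: the two pass rules compared.** Take the Data Analysis rule, for RR, to mean that the absolute mean error and the SD are both at most 5. That is one possible reading of it. In 5,000 simulated test sets per size, with true error SD 2.0, it passed every time at n = 50, 100, 250 and 500. The Table 2 rule passed in 53%, 29%, 5% and 0.1%. With true SD 4.0, where p = 2Φ(5/4) − 1 = 79%, the mean/SD rule still passed in at least 99% of simulations, and the Table 2 rule in 0.02% or fewer.

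**Step 4: a proportion rule, for illustration.** Require the exact one-sided 95% lower bound on the proportion within 5 breaths/min to be at least 95%. The smallest sizes that meet it are 59 children with 0 exceedances (bound 95.05%), 93 with 1 (95.00%) and 124 with 2 (95.01%). At n = 100 one exceedance is allowed. At SD 1.8 the chance of passing is 0.5776 + 100 × 0.00547 × 0.99453⁹⁹ ≈ 0.90, against 58% under the zero-failure rule. At n = 250, six are allowed and the chance exceeds 99.9%, against 25%. Between these two sizes, the larger test set now helps a good app.

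**The case against.** The strongest objection is that the sample maximum may not decide anything. Data Analysis states its own rule, and read as both values at most 5 it does not get harder with n. This stands in part. A reader might infer that the RR verdict will in fact turn on the test-set size, so that an app passing a small test set would fail a large one. The documents do not support that as a certainty: they give two incompatible rules, and the figures above are probabilities. The objection does not rescue Table 2, because a mean/SD rule cannot show that every reading lies within 5.

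The SDs are assumed, and below about 1.25 the dependence on n almost disappears. This stands and limits the size of the problem. The direction, and the fact that 100% cannot be demonstrated, do not depend on the SD.

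A reader might also infer that one miscount by the nurse fails a perfect app. That goes too far. Vital signs may be measured twice in a session, recordings may be repeated, and implausible or problematic readings are excluded. The documents give no error SD for the manual count. But with those exclusions undefined, removing one reading can turn a fail into a pass under a zero-failure rule.

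Nor do the documents show that the split will be chosen to secure a pass. They tie it to data quality.

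The standard met by approved monitors explains where the target came from. It does not say how a finite test set demonstrates it. Confidence bounds are often left to an analysis plan, but here the article itself fixes the criterion and a conflicting pass rule.

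**Conclusion.** The point holds in this form. The Table 2 criterion for RR becomes harder to meet as test readings are added, the number of readings is left open, and the stated pass rule contradicts the criterion. The size depends on an error SD that the documents do not give: negligible at SD 1.25 or less, 96% falling to 81% between 50 and 250 readings at SD 1.5, 76% to 25% at SD 1.8, and 54% to 4% at SD 2.0. These figures assume independent, unbiased normal errors. That 100% cannot be demonstrated, and that the two rules disagree, needs no assumption about the SD. The plan should be changed, but the documents do not establish that the RR result will be wrong.

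**What to change.** 1. **Sample Size.** Fix the test set by child and lock it before any result on it is seen. Define excluded readings at the same time.
2. **Table 2.** Keep the limit of 5 breaths/min. Judge RR by the proportion of readings within it, with an exact one-sided 95% lower bound, using one reading per child or a bound adjusted for clustering. State the required bound and justify it beforehand. The 95% in the working is only an illustration; the sponsor must choose the value.
3. **Data Analysis.** Remove the mean/SD pass rule for RR and refer to the Table 2 criterion. Mean error and SD can still be reported descriptively.
4. **Reporting.** Still state whether the published 100% target was met, and list the largest error, every exceedance and every excluded reading.

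The cost is an edit in three places, with no new data: the illustrative 59, 93 or 124 children all fit within the share that can be held out. The claim becomes less favourable than 100%. The change also relaxes a predefined target. Recruitment is complete and held-out data were to be checked during collection, so if those data have been examined, the change must be disclosed as made after those looks.

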### Participants and Recruitment

Approximately 500 pediatric patients are being recruited at the Sunderland Royal Hospital pediatric emergency department of the South Tyneside and Sunderland National Health Service (NHS) Foundation Trust. All pediatric patients (younger than 18 years of age) attending the pediatric emergency department are potentially eligible for the study. The exclusion criteria are critical illness (as judged by the treating physician), including unconscious patients, patients who were noncompliant in terms of excessive movement during the VS measurements, and patients whose parents, guardians, or carers do not speak English (required to give informed consent). The study aims to recruit according to age, sex, Fitzpatrick skin tone, and medical history criteria, as subsequently described.

The research nurse approaches the parents, guardians, or carers of potential participants identified by the clinical team about taking part in the study. Potential participants aged 17 or 18 years or the parents, guardians, or carers of younger children are provided with an ethics-approved information sheet explaining the study aims, what is involved, and the requirements for participation. Younger children also watch ethics-approved age-appropriate videos (for ages 5-10 and 11-16 years) explaining the study on a tablet device (Multimedia Appendices 4 and 5).

The information sheet and videos were developed in collaboration with the Young People Advisory Group North England and the South Tyneside and Sunderland NHS Foundation Trust Young Persons Group. These groups also provided feedback on the design of the study, consent/assent forms, and other study documents at 2 in-person meetings.

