### Data Analysis

All statistical analyses will be performed using Python (Python Software Foundation). Training data will be used for machine learning to improve the performance of Lifelight Junior for measuring VS in pediatric patients. Appropriate machine learning models will be developed according to the data collected. This is likely to include signal processing and measurement algorithms for PR and RR, and multilayer neural network-based approaches for BP, similar to those used in the adult version of the app.

The separate set of test data will subsequently be used to determine the performance of the app for measuring VS in pediatric patients. Correspondence between VS measurements predicted by the app and the measurements taken manually using SOC methods will be compared using regression coefficients, mean error, and SD, and compared against the performance targets set out in Table 2. An accuracy target will be considered met if the mean error and SD for the app measurements are at least equal to the target (Table 2). Heat maps or scatter plots will also be developed.

Linear regression will be used to assess the impact of skin tone on the accuracy of the app for measuring each VS, using the Fitzpatrick skin tones as the explanatory variable.

Quantitative data from the questionnaires will be summarized. Thematic analysis will be used to analyze free-text responses to identify perceptions of the app and variations in the way patients, their parents or carers, and health care professionals interact with it and any challenges they encounter.

All analyses will be completed per protocol since there is no intention to treat. There will be no imputation of missing or implausible data, and any missing, implausible, or problematic readings will be excluded from analysis.

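### Under the stated pass rule, an app that outputs one constant oxygen saturation could meet the 4% target, because the rule tests only mean error and SD and no quota guarantees low readings

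*Protocol article*

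**What the plan says.** Oxygen saturation is one of the three vital signs in the primary objective (Introduction). In Performance Targets, Table 2 gives its target as "Maximum error tolerance 4" percent. The entry names neither the statistic being bounded nor the range of saturation over which it applies. The respiratory rate entry in the same table is more explicit: "Maximum error of 5 breaths per minute for 100% of measurements".

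Data Analysis says that app and standard-of-care values will be "compared using regression coefficients, mean error, and SD, and compared against the performance targets set out in Table 2". It then gives one decision rule for all three signs: "An accuracy target will be considered met if the mean error and SD for the app measurements are at least equal to the target". I read this as mean error and SD no worse than the target. Table 2 attaches no limit to the regression coefficients, and the rule does not mention them.

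Three passages bear on which saturations will be in the sample:

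- Participants and Recruitment: "The exclusion criteria are critical illness (as judged by the treating physician), including unconscious patients".
- Sample Size, Table 3: "≥40% in each of the following categories", the categories being febrile, afebrile, ill and well. Acute respiratory illness has a ceiling and no floor: "no more than 50% of recruited patients will have an acute respiratory illness". No quota is defined by saturation.
- Results: "The performance of the app will be determined across the range of VS values encountered in children in clinical practice".

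**The concern.** A tolerance of 4 points is wide relative to the part of the scale where most children's saturations are likely to lie. If the reference values are tightly grouped, a small pooled mean error and SD say little about whether the algorithm responds to saturation at all: an output carrying no information would score well too. The few children with low saturation would be misread by many points, and their errors would be diluted by the majority.

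At stake is the meaning of a pass. The article intends accuracy to be shown over the range of values seen in practice, and its Discussion presents the app as a way to pick up early deterioration. A pass obtained on a narrow range would support neither.

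**Working it through.** There is no figure in the plan to reproduce. The Sample Size section says the number cannot be formally calculated, and the article gives no expected mean or SD of saturation.

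**Step 1: what a constant scores under the Data Analysis rule.** Let the app always output c. The error for a child with reference saturation S is c − S, so

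- mean error = c − mean(S);
- SD of error = SD(S).

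With c at the mean of S, the mean error is 0 and the rule is met whenever SD(S) ≤ 4. A c taken from training data also serves, provided it lies within 4 points of the test-set mean. Because an SD cannot exceed half the range, a pass is certain if all reference values lie within an 8-point span, for example 92 to 100.

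**Step 2: is SD(S) ≤ 4 plausible?** This needs an assumed distribution. Most children: normal, mean 98, SD 1.2. A low-saturation group: mean 92 (SD 2), 90 (SD 3), 88 (SD 3) or 85 (SD 4). Values are rounded and capped at 100. The simulated error SD of the constant is:

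| Share low | Low mean 92 | 90 | 88 | 85 |
|---|---|---|---|---|
| 0% | 1.2 | 1.2 | 1.2 | 1.2 |
| 5% | 1.8 | 2.2 | 2.6 | 3.2 |
| 10% | 2.2 | 2.8 | 3.3 | **4.2** |
| 20% | 2.8 | 3.6 | **4.4** | **5.6** |

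Bold entries fail.

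A second mixture can be checked by hand. Take most children at mean 97.5 (SD 1.2) and a low group at mean 88 (SD 1), 9.5 points lower.

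- 5% low: mean = 0.95 × 97.5 + 0.05 × 88 = 97.03. Variance = 0.95 × 1.44 + 0.05 × 1 + 0.95 × 0.05 × 9.5² = 5.70, so SD = 2.39.
- 10% low: mean = 96.55. Variance = 0.90 × 1.44 + 0.10 × 1 + 0.90 × 0.10 × 9.5² = 9.52, so SD = 3.09.

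Both pass, while the low children are misread on average by 97.03 − 88 = 9.0 and 96.55 − 88 = 8.6 points.

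**Step 3: where the constant stops passing.** With two points only, 98 and L, SD = (98 − L) × √(p(1 − p)), where p is the share low. This reaches 4 at p = 50% for L = 90, 20% for L = 88 and 10.6% for L = 85. For L = 92 the largest possible SD is 3, so it never does.

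**Step 4: the other reading of Table 2.** Suppose the 4 points bind every reading. A constant that must also cover readings up to 100 does best at 96, which covers 92 to 100. It passes only if no test reading is below 92. With q the share below 92 and n test readings, the chance is (1 − q)^n. The article does not fix n, so three sizes are shown:

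| q | n = 50 | n = 100 | n = 250 |
|---|---|---|---|
| 1% | 0.61 | 0.37 | 0.08 |
| 2% | 0.36 | 0.13 | 0.006 |
| 5% | 0.077 | 0.006 | about 0 |

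The two passages therefore lead to opposite results for the same uninformative output in many settings.

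**The case against.** The strongest reply is that Table 2 speaks of a maximum. Taken literally, one reading below 92 defeats the constant, and the source cited in the table may define the statistic and range. This stands in part: Step 4 shows that the literal reading is usually protective. But the only decision rule in the article uses mean error and SD, so the literal reading cannot be assumed.

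A second reply is that the sample may well contain low saturations. A reader might infer from the exclusion of critical illness that no recruitment stratum supplies them. The article does not support that. Recruitment is in a pediatric emergency department, at least 40% must be ill, and conditions such as bronchiolitis and pneumonia are admitted up to half the sample. What can be said is that no quota guarantees low readings.

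Third, the planned regression coefficients and scatter plots or heat maps would expose a constant, which gives a slope of zero and a flat plot. That is correct, so it would go too far to say that the planned analysis cannot reveal the problem. The point is that none of these outputs enters the pass rule.

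Fourth, an article need not carry every reporting detail. Agreed; the absence of banded tables alone would not be a finding. The finding is about the rule that is stated.

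A reader might also extend the point to pulse and respiratory rate, where age alone creates a wide range. The targets do not support that. For pulse rate, an age-only predictor with an assumed within-age SD of 12 to 15 has a root mean square error of about 12 to 15, well above the limit of 5. Its correlation would be flattering, but no target attaches to correlation. For respiratory rate, a limit on all measurements is hard for any uninformative predictor to meet.

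**Conclusion.** The concern holds for oxygen saturation under the mean-error and SD rule. That a constant passes whenever the reference SD is 4 or less is algebra. That the SD will be 4 or less is an assumption. It holds in all mixtures examined with up to 5% low-saturation children, and in those with 10% low unless the low group averages about 85. It fails with 20% low once the low group averages 88 or below.

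Separately, and without any assumption, the maximum in Table 2 and the mean and SD in Data Analysis are different criteria for the same target and must be reconciled.

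It does not follow that the saturation algorithm will be uninformative, or that the sample will lack low values. The conclusion is only that a pass, as defined, would not rule out an uninformative output. The point should be settled before the final test-set analysis; it does not put the data collection in question.

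**What to change.** Before the final test-set analysis:

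1. Reconcile Table 2 with Data Analysis by stating which statistic the 4% bounds for oxygen saturation.
2. Report saturation error by prespecified band of reference saturation, with the number of readings and a 95% confidence interval in each band.
3. Add to the pass rule that the app's root mean square error for saturation must be lower than that of a constant predictor, taken as the training-set median.
4. Limit any saturation accuracy claim to the reference range observed with adequate numbers.

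If the division into training and test data is still open, stratify it by reference saturation. Placing the low-saturation children mainly in the test set is not advisable: the Results section says that training is already under way, so moving children now risks overlap between the two sets, and it would deprive the algorithm of the scarce values it needs to learn from.

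The cost is analysis wording, one banded table and one benchmark row. No new participants or procedures are needed. The downside is that the saturation claim may have to be narrowed.
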